## Methods/design

### Pilot trial aims

This pilot trial aims to determine the optimum methods for testing the effectiveness of a bespoke model of group antenatal care, called ‘Pregnancy Circles’, in a UK NHS setting serving populations with high levels of social deprivation and cultural, linguistic and ethnic diversity. It will inform the protocol for a full randomised controlled trial of the Pregnancy Circles model. The pilot trial will be undertaken to include an assessment of:Methods of recruitment, recruitment rates, and reasons for declining participation;Retention in groups and reasons for drop out;Data collection for outcome assessment;Approaches to language support for intervention and research purposes.

An additional aim will be the further development and refinement of the Pregnancy Circles model of group antenatal care for culturally, linguistically, ethnically and socio-economically diverse communities. This will include determining the extent of the linguistic diversity that can be incorporated in a single Pregnancy Circle. The pilot trial will also aim to determine the suitability of our proposed primary outcome measure (spontaneous vaginal birth) and to develop a composite measure of a ‘healthy birth’ for the economic evaluation.

### Intervention

Following an extensive feasibility study, Pregnancy Circles are being implemented by a London NHS Trust as part of its service development. Initially, this was on a small-scale basis (four test groups in the feasibility work, followed by the three groups that form the focus of this pilot trial). Each Pregnancy Circle will consist of between 8 and 12 pregnant women who have estimated delivery dates within the same approximate 2- to 4-week period. The women who consent to participation in the study will be randomly assigned to one of two trial arms. One arm will receive standard antenatal care, whereas the other will receive all of their usual midwife-led antenatal care within a Pregnancy Circle. Any necessary appointments for consultant or specialist care will be carried out as per the usual care pathways outside of (and in addition to) the Circle.

Those women randomised to the group, antenatal care will start attending the ‘Pregnancy Circle’ for the first time at the routine midwife appointment (approximately 16 weeks of pregnancy) that follows their antenatal booking appointment (this usually takes place between 8 and 12 weeks of pregnancy). Subsequently, the women will continue to attend the Circle according to the normal antenatal care schedule. Any woman who chooses to discontinue her care in a group during pregnancy will transfer to the conventional care pathway. Any woman who does not attend the first Circle will be contacted by the facilitating midwives to ascertain the reasons for this. If non-attendance is due to pregnancy loss, they will be referred, by the facilitating midwives, to sources of ongoing support, such as their GP, as appropriate.

Each Pregnancy Circle group session will be facilitated by two midwives supplemented with bilingual health advocates or other support staff as appropriate. The same two midwives will facilitate all the sessions for a Pregnancy Circle, and each woman will have one of these midwives as their lead midwife. Women participating in the ‘Pregnancy Circle’ who are having their first child will receive the same number of antenatal appointments as women receiving standard care. Women having subsequent children will be offered the same number of antenatal appointments as women having their first child, therefore receiving two additional appointments to the standard model for women having subsequent children. All women attending the ‘Pregnancy Circle’ will receive standard postnatal care but will also be invited to a postnatal reunion session held approximately 1 month after the last antenatal appointment (40 weeks of pregnancy). A local health visitor will co-facilitate this reunion postnatal session with the midwives. Women in the control group will continue to have standard postnatal care and then standard health visitor care.

There will be a total of eight antenatal group sessions each of which will last for approximately 2 h. The first part of each session will involve ‘self-care activities’ (e.g. women will be taught how and encouraged to take an active part in their care by testing their own urine, taking their own/each other’s blood pressure and writing the results in their notes). Following these checks, the sessions will involve short one-to-one sessions with one of the midwife facilitators for individual health checks (e.g. abdominal palpation) whilst the rest of the group has a group discussion facilitated by the second midwife. Any concerns regarding a group member’s blood pressure or scan or test results, or any individual psychological or social issues, can be addressed during the individual health check or at the end of a session by a woman’s lead midwife, whilst the other midwife continues facilitating the group. The content of group discussions will be woman-led, supplemented as appropriate by the facilitating midwives to ensure that essential topics are covered, as per national and local guidelines. As with usual care, women will be referred to other specialist services for routine and additional appointments, blood tests and scans as appropriate. The postnatal session will use a similar approach and format, but with a focus on maternal postnatal well-being and the well-being of the baby and infant feeding support.

Midwife and health visitor facilitators will be documenting the appointment in the same way they usually would. During the first group session, the facilitating midwives will develop ground rules of confidentiality, asking the participants to respect each other’s privacy and confidentiality regarding what is shared within the group. The views of the group on how and when partners are involved in the sessions will be ascertained.

Pregnancy Circles model is a ‘bespoke’ model of antenatal care, designed to be flexible in order to allow the midwives and women to adapt it to suit local need—this may include the inclusion of external speakers, involving student midwives or other appropriate observers, or making adaptations for women with language or other needs.

### Study setting

The pilot trial will be carried out within the maternity services of an inner London acute NHS Trust. This Trust provides services primarily to residents of three London boroughs. One Pregnancy Circle (i.e. one group of women who have their antenatal appointments together) will be run within each of these three boroughs by midwives from the local service. The exact area within each borough in which the Pregnancy Circles will be run will largely be determined by practical issues, with decisions being made in consultation with service managers. The Circles will run in the usual working area of the midwives who facilitate them.

### Trial design

A UK-based external pilot randomised controlled trial will involve two parallel arms: one receiving a group model of antenatal care (Pregnancy Circles) and the other receiving usual care. It will not be possible for participants or maternity staff to be blinded to allocation. Researchers conducting process evaluation observations and interviews will also be unblinded. Data informatics staff supplying outcomes information from electronic records and those conducting the statistical analysis will be blinded to the intervention allocation.

#### Inclusion criteria

Eligibility will be assessed by a researcher or research midwife within the antenatal booking clinic. Those who will be eligible include:Women who are currently pregnant and registering (or registered) for antenatal care at the participating NHS Trust maternity servicePrimiparous and multiparous womenAll pregnant women, regardless of the risk category applied to their pregnancy (both ‘low’ and ‘high’ risk pregnancies included)Women who live within the working areas of the local midwife group facilitators and have an estimated delivery date that fits with those of a proposed group

The pilot will test groups with a limited diversity of languages spoken and groups with greater linguistic diversity (e.g. with one to three additional languages other than English). Thus, the recruitment for different Pregnancy Circles will have different inclusion criteria with respect to particular languages spoken.

#### Exclusion criteria

The following are the exclusion criteria:Non-pregnant womenWomen registered for antenatal care at other NHS TrustsPregnant women who live outside the local target areaPregnant women whose estimated delivery dates do not fit with those of a proposed groupPregnant women who, at the time of antenatal booking, will likely not be able to participate at the proposed group start date and/or throughout the entire seriesPregnant women who are under 16 years of age at the time of recruitmentPregnant women with a documented learning disabilityPregnant women who speak a language that is not a target language for the group being recruited at the time of their potential recruitment

### Sample size

The study will aim to recruit 24 participants from each of the three maternity units within the participating NHS Trust making a combined total of 72 women. Half of the recruited women in each area (up to 12 women) will be randomised to take part in the ‘Pregnancy Circles’ and half to receive standard antenatal care. This sample will not be powered to show differences between the trial arms on outcomes. Rather, the sample size has been determined to allow us to test the assumptions used in the sample size calculations for a full trial. This sample size will allow recruitment to take place in the three geographical areas in the NHS Trust where the Pregnancy Circles will take place, to allow us to test recruitment rates and to assess whether this differs by area. It will also allow us to explore uptake and retention rates to see whether our assumptions about the loss to follow-up are appropriate.

### Recruitment of participants

Potential participants will be recruited from women attending their first midwife appointment to register with the NHS Trust maternity services (the ‘booking appointment’, which usually takes place when women are between 8 and 13 weeks pregnant). The research team will work with the antenatal booking clerks in each area to identify women who fit the inclusion criteria prior to the booking appointment. The participant information leaflet (PIL) about the REACH Pregnancy Circles study and an introductory letter will be included with the mailed booking appointment confirmation letter to these women.

Recruitment and consent will be carried out by REACH researchers and research midwives employed by the NHS Trust. Once attending their booking appointment, all women who fit the inclusion criteria will be approached by a researcher in the waiting room. An additional copy of the PIL will be provided. A verbal explanation of the Pregnancy Circles, the study and the concept of randomisation will also be given by the recruiter, and women will have the opportunity to ask questions, using interpreting services where appropriate.

Women who decline to participate in the pilot trial will be invited to take part in a brief (5-min) interview on their understanding of group antenatal care and their reasons for declining to participate. If they provide verbal consent to this 5-min interview, an anonymous proforma will be used to record their responses as well as basic demographic information and the date and venue of the clinic. These data will inform recruitment procedures for the potential future full trial. The interview will be with a researcher/research midwife at the time they decline to take part. It will be made very clear to women that their views will be used to inform efforts to recruit to future groups and that they are not being asked to justify or change their decision.

If a woman is unsure about whether she wishes to participate in the trial, she will be able to contact the researcher after the booking visit. She will be given a copy of the consent form and baseline questionnaire to take away to be completed at home if she decides to participate. Stamped addressed envelopes will also be provided. She will be asked if she is happy to give her telephone number/email address to the researcher so that a reminder contact can be made to clarify whether she is interested in participating. If a woman does not wish to give this contact information, she will have the option to telephone the research team using the number given on the PIL.

Women who choose to participate in the ‘Pregnancy Circles’ will be asked to sign a consent form and to fill in a self-completed baseline questionnaire. Language support, as described below, will be offered for the completion of both, if required. It will be explained in writing and verbally that they can withdraw at any time if they so wish.

### Language support

The study population is extremely diverse in terms of languages spoken. We will use the pilot trial to test out the feasibility and acceptability of different forms of language support. The principal forms of language support we plan to use in the trial are (1) bilingual health advocates employed by the NHS Trust^1^, (2) language line (a telephone interpreting service) and (3) bilingual advocates from an external agency.

We are particularly focussing on working in partnership with the health advocacy service within the NHS Trust which will be funded to provide services for the trial. This will include providing advocates to work alongside a researcher supporting recruitment and consent, telephone follow-up and questionnaire completion in clinic, community and home settings. Advocates will also work one-to-one with women in the Pregnancy Circles. We aim to provide training sessions about the research for the Trust’s health advocates as well as the staff who book advocates and attend meetings to facilitate joint working. We expect there to be occasions when an appropriate advocate is not available from the service, including when an eligible woman presents who speaks a language that is unusual for the area. In these instances, language line will be used for recruitment, and an external health advocate will be found to support further involvement.

### Randomisation

Participants will be allocated to Pregnancy Circles or usual care in a one-to-one ratio. Block randomisation will be carried out by a statistician in the Pragmatic Clinical Trials Unit (PCTU), independent of the trial. Randomisation will be stratified by the estimated delivery date and the location of the Pregnancy Circle. The research team will notify the woman verbally and in writing of her allocation and working with booking clinic staff will confirm either her next appointment date and time (for women allocated to the control group) or the full list of dates, times and venue for the Pregnancy Circles (intervention group).

### Pilot trial feasibility outcomes

Data will be collected on recruitment; uptake of, and retention in, the Pregnancy Circle groups; and outcomes data collection rates. Figure 1 highlights the assessments that will be completed by participants, as per the SPIRIT Statement [33].

**Fig. 1 Fig1:**
[figure not shown]
Schedule of enrolment, interventions and assessments. SPIRIT diagram for REACH Pregnancy Circles pilot study

The different rates achieved in the pilot will enable estimates to be made for a full trial. Additionally, they will inform decisions about changes that need to be implemented and the appropriateness of progression to such a trial; this process will be undertaken in conjunction with the Programme Steering Committee (see Table 1). ‘Red light’ rates will halt the progression, unless suitable solutions can be implemented.(i)*Recruitment figures* will be kept for each antenatal booking clinic session attended by the research midwives via a proforma, regarding numbers of women eligible, number approached, number who declined and number who consented. No identifying information will be recorded. Approaches used for language support will be recorded.(ii)*Uptake and retention to the intervention* will be derived from records kept by the midwives who are facilitating the Pregnancy Circles, who will record attendance at each group using a paper proforma, which they will pass on to the research team. The research team will transfer this information to a password-protected electronic database and replace names with study IDs. The paper proformas will then be destroyed. Midwives will have a protocol to follow for women who choose not to participate in the Circle, at any point through the intervention, to ensure that all women receive antenatal care.(iii)*Questionnaire completion rates will be used to assess* the potential burden of data collection for participants. We will explore completion rates at each of the two follow-up points and whether each measure within the questionnaire is completed in a way that provides useable data. We will explore the questionnaire completion rates for women who required a bilingual advocate, to provide further information about the appropriateness of our research tools. Additionally, this will be assessed through open questions during one-to-one interviews with participants (see the “Process data—views about trial methods and the intervention” section below). More detail is provided on the questionnaires in the “Participant outcomes data collection” section below.

#### Process data—views about trial methods and the intervention

Process data will also be collected from participants and key stakeholders to assess the feasibility of the proposed methods for the full trial of ‘Pregnancy Circles’. The aim of this data collection will be to help explain the reasons behind any challenges with recruitment, uptake, retention and outcomes data collection and to provide solutions for improvement. This data will be collected through process questions added at the end of the outcomes questionnaires (see Table 2) and one-to-one interviews with a small sample of women and staff.

**Table 2 Tab2:** Data measures for Pregnancy Circles pilot

Baseline measures (12 weeks pregnant)	Outcomes questionnaire 1 (35 weeks pregnant)	Postpartum maternity records audit	Outcomes questionnaire 2 (4 months postpartum)
Social support (Duke Social Support Scale) Self-efficacy (Pearlin Mastery Scale) Prenatal stress (Revised Prenatal Distress Questionnaire) Health service usage maternal self-report of their use over the previous 4 months of a variety of primary health services (GP, health visitor, social work and hospital doctor), A&E services, antenatal admissions. Demographic questions • Age • Ethnicity • Language • Parity • Education • Tenancy	Women’s satisfaction with care (questions from the Care Quality Commission’s Maternity Survey) Social support (Duke Social Support Scale) Self-efficacy (Pearlin Mastery Scale) Involvement in decisions about care (Picker Institute’s Experience with Maternity Services questionnaire) Prenatal stress (Revised Prenatal Distress Questionnaire) Health service usage maternal self-report of their use over the previous 4 months of a variety of primary health services (GP, health visitor, social work and hospital doctor), A&E services, antenatal admissions. Attendance at antenatal education classes (NHS; other) Process questions • Randomisation feelings *For intervention:* • Attendance • Reasons for non-attendance • Perceptions of the group experience	Spontaneous vaginal birth (*primary outcome*) Attendance at ANC (number of regular appointments attended) Caesarean delivery (planned, emergency, none) Epidural/spinal analgesia use in labour Infant birthweight, defined as low if less than 2500 g Gestational age at delivery, dichotomized as term or preterm (less than 37 weeks) Breastfeeding initiation	Women’s satisfaction with care (questions from the Care Quality Commission’s Maternity Survey) Social support (Duke Social Support Scale) Self-efficacy (Pearlin Mastery Scale) Involvement in decisions about care (Picker Institute’s Experience with Maternity Services questionnaire) Breastfeeding continuation and exclusivity Health service usage maternal self-report of their use over the previous 4 months for themselves and their baby of a variety of primary health services (GP, health visitor, social work and hospital doctor), A&E services, late antenatal admissions, and uptake of infant immunisations at 2 and 3 months). Postnatal depression (Postpartum Depression Screening Scale) Process questions • Perceptions of the impact of ANC on birth/postpartum • Views of trial procedures

The process evaluation will include the following components:*Five-minute interview and anonymous proforma for women who decline to take part in the study*, as described in the ‘Recruitment of patients’ section above.
*Interviews with Pregnancy Circle participants*

At the final antenatal group session, participants in the Pregnancy Circles will be offered the opportunity to have a one-to-one semi-structured interview after their baby has been born. This will last 30–60 min and will be conducted either face-to-face or via the telephone according to participant preference. A purposeful sample of approximately 20 participants will be interviewed, at a time (probably around 6 weeks postnatal) and location of their choice. Women may choose to have their partners and/or children with them during the interview. Women who have suffered an adverse neonatal outcome (neonatal death, admission to the neonatal unit) will not be interviewed unless they specifically request it. The facilitating midwives will confirm whether women who had previously consented to the interview can be contacted postnatally. The purpose of the interviews will be to explore their experiences and satisfaction with this model of antenatal care and their perceptions of its effects, as well as their views on recruitment, randomisation and data collection methods. The views and experiences of women who received language support will also be sought.c)
*Interviews with women who leave the ‘Pregnancy Circles’*

Women who discontinue with a group during pregnancy will be invited to participate in an interview (up to 30 min, in person or by telephone depending on preference). Women who suffered pregnancy loss will not be approached for these interviews. The purpose of the interviews will be to explore the reasons the woman has decided to leave the group, and if relevant, explore how the group failed to match the women’s expectations, including the content, convenience and conduct of the sessions. The interviews will elicit suggestions for future groups and explore women’s views about randomisation to this kind of care.d)
*Interviews with facilitating midwives and other staff involved with ‘Pregnancy Circles’*

In order to provide context to data collected from women, a purposeful sample of midwives and other relevant staff at the participating NHS Trust will be offered the opportunity to take part in a brief (up to 30 min) interview about their perceptions of the recruitment and randomisation procedures, the data collection methods (e.g. timing) and issues relating to delivery of and retention in the Pregnancy Circles. Interviews with midwives will include questions pertaining to potential contamination of usual care by the introduction of Pregnancy Circles care.

Information about the process evaluation participants (name, contact details, demographic details) will be stored on a participant information database on the secure server at City University London. Study ID numbers will be used on collected data to ensure anonymity. Signed consent forms for process data collection will be stored separately in a locked filing cabinet in the office of the research team at UEL, which requires an access code to enter. The interviews will be transcribed verbatim, and the confidentiality of personal data will be ensured through the use of anonymisation and pseudonymisation techniques. All audio recordings and transcripts will be stored securely in a locked filing cabinet, in a locked office, that only members of the research team will have access to. Transcribers will be bound by a confidentiality agreement.

All qualitative interview data will be entered into the data analysis package NVivo, which will be used to manage and code data. The data will be subjected to thematic framework analysis. Codes will be applied line by line to transcripts, which will identify key themes and how these inter-relate in order to develop an analytical framework.

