#### Outcomes questionnaires general overview

The questionnaires will be administered as online and hard copies, with participants able to select their preferred mode. The research team will use a database to track the sending out and return of hard copies. To facilitate online surveys, an electronic participant-recorded outcome tool, provided by the PCTU, will be used. This will have the facility to email participants a link to questionnaires. All women will be offered a £10 voucher for each of the three questionnaires they complete. These will be handed to women who complete their questionnaire in the presence of a researcher and posted to women who submit their questionnaire without a researcher being present.

The questionnaires will be identified only with study ID number. The hard copies of the questionnaires will be stored in a locked filing cabinet in a pin code accessible office for the duration of the study. Data will be entered onto a database developed and maintained by the PCTU. For hard copy questionnaires, research team staff will do full double data entry for the primary outcome and double data entry on a 10% sample for other outcomes. Depending on identified error rates, the proportion of data double entered may be increased.

The participants’ questionnaires will be completed at three time points: baseline (8–12 weeks pregnant), first follow-up questionnaire (35 weeks pregnant) and second follow-up questionnaire (approximately 4 months after the baby is born). The baseline questionnaire will include demographic questions, a limited number of outcome measures and some questions relating to service preferences. The follow-up questionnaires will include outcome measures and some process questions relating to randomisation, attendance at antenatal care and preferences for providing outcomes information, see Table 2 for details on the questionnaires.

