In the pilot trial, the economic evaluation will explore alternative utility measures via the participant questionnaires. Additionally, we will involve women in defining what a ‘healthy birth’ is, so that we will be able to calculate the incremental cost per additional healthy birth for group antenatal care compared to control, using this composite measure. In the early months of the pilot, we will work in consultation with our lay co-investigators and with the local Maternity Services Liaison Committees, to determine whether the suggested questions to be used in the follow-up questionnaires to capture women’s satisfaction with antenatal care are sufficient, or whether additional ones need to be included. Responses to antenatal care satisfaction questions plus relevant outcomes data will be included in the composite. Initially, we will conceptualise a ‘healthy birth’ as occurring if women:Were largely satisfied with their care during pregnancyFelt involved in decision-making about their careHad low antenatal distressDid not suffer postnatal depression (within the follow-up period)Perceived that they had good levels of information and professional support (during pregnancy, labour and delivery)Had a baby with gestational age at delivery, ≥ 37 weeks.Did not have a caesareanHad a baby with a birthweight > 2500 gFelt their care was responsive to cultural, religious/spiritual and linguistic needs (i.e. individualised, culturally sensitive care).

We will use the data collected during the pilot to assess the validity of this composite measure and to develop algorithms for how births might be classified on a continuum from ‘healthy’ to ‘unhealthy’.

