Our assumption for the full trial is that costs will include the cost per pregnant woman of group antenatal care as well as mother and infant primary and secondary care costs from conception until 4 months postpartum. As such, in this pilot trial, use of primary and secondary care will be collected via additional questions on the participants’ baseline and follow-up questionnaires. Unit costs will be obtained from published national sources. Confidence intervals and cost-effectiveness acceptability curves will be calculated using bootstrapping (sampling with replacement). The perspective we will adopt for the economic evaluation will be health and social care costs. We will validate our resource use data as part of the pilot study by checking resource use reported by women in a sample of questionnaires against medical records. For the sensitivity analysis, we will use non-parametric bootstrap to construct confidence intervals for trial data: one-, two- and multi-way deterministic analyses for any assumptions made; if a decision model is constructed, we will do a full probabilistic sensitivity analysis. Trial missing and censored data will be handled the same way in the economic evaluation as for the statistical analysis.

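### As listed in Table 2, the fixed 4-month recall windows leave about 19% to 26% of the conception-to-4-months-postpartum costing period unasked for most service contacts

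*Protocol article*

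**What the plan says.** The Economic evaluation section sets the full-trial cost scope, beyond the cost of group care itself, as "mother and infant primary and secondary care costs from conception until 4 months postpartum". It then gives this as the reason why, "in this pilot trial, use of primary and secondary care will be collected via additional questions on the participants"' baseline and follow-up questionnaires.

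The section Outcomes questionnaires general overview fixes the first two time points as "baseline (8–12 weeks pregnant), first follow-up questionnaire (35 weeks pregnant") and the third at roughly 4 months after birth. The Table 2 header puts baseline at 12 weeks.

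Table 2 gives the recall window. At baseline and at 35 weeks it is "maternal self-report of their use over the previous 4 months". At the postpartum questionnaire it is "maternal self-report of their use over the previous 4 months for themselves and their baby", and that entry also lists "A&E services, late antenatal admissions, and uptake of infant immunisations at 2 and 3 months".

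On utilities, the Economic evaluation section says that "the economic evaluation will explore alternative utility measures via the participant questionnaires". Table 2, to which the overview refers the reader for questionnaire details, lists no utility measure in any column.

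**The concern.** A total cost over a defined period needs recall windows that together cover that period and stop at its edges. Here every window has the same length, while the spacing between questionnaires is 23 to 27 weeks and then about 22 weeks. Fixed 4-month windows (about 17.4 weeks) cannot meet end to end on that schedule, and the first one runs back past conception.

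The pilot exists to find out whether usable full-trial data can be collected. Completion rates would not expose this fault: a woman can answer every question fully and still never be asked about the missing weeks. The wording could therefore pass the pilot and go into the full trial unchanged.

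**Working it through.** The documents state no coverage figure, so there is none to reproduce. The check is interval arithmetic.

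**Inputs from the protocol**
- Window W = 4 months = 4 × 365.25/12 ÷ 7 = 17.39 weeks (Table 2).
- Baseline at 8–12 weeks (questionnaire overview); 12 weeks (Table 2).
- First follow-up at 35 weeks; second at about 4 months after birth.
- Circles start at about 16 weeks (Intervention section).

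**Assumptions**
- Conception at gestational week 2 and birth at week 40.
- The late-admissions item reaches back to week 35.

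**Costing period**
- (40 − 2) + 17.39 = 55.39 weeks.

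**Gap 1, baseline to the opening of the 35-week window**
- The window opens at 35 − 17.39 = 17.61 weeks.
- Baseline at 12 weeks: 17.61 − 12 = 5.61 weeks.
- Baseline at 8 weeks: 17.61 − 8 = 9.61 weeks.

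**Gap 2, 35 weeks to birth**
- The postpartum window opens at about birth, so the gap is 40 − 35 = 5 weeks.

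**Share of calendar time unasked: GP, health visitor, social work, hospital doctor, A&E**
- Baseline at 12 weeks: (5.61 + 5)/55.39 = 10.61/55.39 = 19%.
- Baseline at 8 weeks: (9.61 + 5)/55.39 = 14.61/55.39 = 26%.

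**Admissions**
- The late-admissions item covers gap 2, so only gap 1 remains: 5.61/55.39 = 10% to 9.61/55.39 = 17%.

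**From the start of the Circles**
- Period: (40 − 16) + 17.39 = 41.39 weeks.
- Unasked: (17.61 − 16) + 5 = 6.61 weeks.
- Share: 6.61/41.39 = 16%. Of the 6.61 weeks, 5 are the end of pregnancy.

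**Part of the baseline window before conception**
- Baseline at 12 weeks: window opens at 12 − 17.39 = −5.39; (5.39 + 2)/17.39 = 7.39/17.39 = 43%.
- Baseline at 8 weeks: window opens at −9.39; (9.39 + 2)/17.39 = 11.39/17.39 = 66%.

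**Sensitivity of the 19% to 26%**

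| Change | Unasked share |
|---|---|
| Birth at 37 weeks | 7.61/52.39 = 14.5% to 11.61/52.39 = 22.2% |
| Birth at 41 weeks | 20.6% to 27.7% |
| Period counted from week 0 | 18.5% to 25.5% |
| Baseline at 13 weeks (latest usual booking time in the Recruitment section) | 17.3% |
| 4 months read as 16 weeks | 22.2% to 29.6% |

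The size moves with the assumptions, but the gap does not close under any of them.

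**The case against.** The strongest reply has four parts.

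**Questionnaires are not the only source.** The abstract says routine maternity data will also serve the economic evaluation, and the section on routine data describes two record routes whose full field lists are not shown. Midwives record attendance at every Circle, and the audit column of Table 2 counts regular antenatal appointments. This stands: a reader might infer that the pilot cannot supply cost data at all, and the documents do not support that. But the audit column lists no GP, health visitor, social work or A&E contacts. The check of reported use against medical records covers only a sample and is described as validation. The gap remains for those contacts.

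**The gaps might be read as missing the weeks when the arms diverge.** That is too strong. Only about 1.6 weeks of gap 1 come after the Circles start, and attendance at the first Circle is recorded separately. After the start of group care, the loss is mainly week 35 to birth.

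**Table 2 is condensed.** It omits the service-preference questions that the text places in the baseline questionnaire, and the full protocol is not shown. A reader might infer that no utility data are collected, or that birth-stay and neonatal-unit days are not captured. Absence from this table does not show either. For utilities there is a stated inconsistency to resolve; for the inpatient days there is not even that. The recall windows are different, because they are stated positively.

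**Fixed 4-month recall is defensible.** It limits recall error, and the public-involvement feedback asked for a short, simple baseline questionnaire. This is a genuine trade-off, but it does not reconcile the windows with the period they are meant to cover.

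**Conclusion.** The recall windows listed in Table 2 do not match the costing period they are meant to serve. About 19% to 26% of calendar time is unasked for most contacts, and about 10% to 17% for admissions. Within the period after the Circles start, about 16% is unasked. The baseline window also collects use from before pregnancy. The late-admissions item conflicts with its own window, which opens at about birth.

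These are shares of time. The documents give no basis for turning them into shares of cost, and the figures rest on the assumed conception and birth weeks.

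Severity is moderate. Costing from conception to 4 months postpartum is a full-trial plan, the pilot is not powered for outcome comparisons, and none of the progression criteria in Table 1 uses cost data. It still merits correction now, because testing the data collection is the pilot's purpose. The utility point is secondary: an inconsistency between the Economic evaluation section and a condensed table.

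**What to change.** Replace the fixed window with dated anchors in the resource-use questions, with the dates pre-printed where known:
- Baseline: since you became pregnant.
- First follow-up (35 weeks): since the date of the baseline questionnaire.
- Second follow-up: since the date of the first follow-up questionnaire for the mother, and since birth for the baby.

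Both gaps then fall to zero and pre-conception use drops out. The late-admissions item no longer conflicts with its window.

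The cost is wording, dates merged into each form, and longer recall: 35 − 12 = 23 to 35 − 8 = 27 weeks at the first follow-up, and 5 + 17.39 = 22.4 weeks for the mother at the second, against 17.4 weeks now. The planned comparison with medical records can measure the added recall error. At baseline, recall becomes shorter.

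Separately, reconcile the statement on utility measures in the Economic evaluation section with Table 2, either by listing the measures and their time points or by amending the text.
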